### Data collection

Potential participants who do not take part (either ineligible or non-consenting) will be recorded on non-registration logs recording age, sex, ethnicity and reason for patient non-registration. These will be collected by local investigators and returned to the CTRU. Baseline variables for registered participants will be collected on paper CRFs by site staff, who will keep copies and return originals to the CTRU (except for consent forms which are kept at site and copies sent to the CTRU). GRACE and CRUSADE risk scores will be estimated for each participant at each participating hospital site randomised to use the GRACE risk score tool and recorded on CRFs. Since the paper nomogram approach is also being used in similar international trials, scoring via mobile phone apps or web-based calculators will not be permitted. Details of medications and tests prescribed and received during hospitalisation will be recorded. At baseline, the participants’ Edmonton frailty score^29^ will be assessed and all participants will complete the EQ-5D-5L questionnaire. At 12 months, surviving participants will be asked to complete and return a further EQ-5D-5L by post.

Follow-up data for hospital healthcare utilisation, and dates and causes of death will be collected using multi-source national electronic health records (EHRs). This will include data capture from the National Institute for Cardiovascular Outcomes Research^25^ suite of nationwide cardiovascular registries,^30 31^ Hospital Episode Statistics,^32^ Office for National Statistics and the National Audit of Cardiac Rehabilitation database.^33^ To obtain records, the CTRU will provide the patient identifiers to the responsible organisations (with patient consent obtained for this data transfer) who will link the identifiers to their records according to their own deterministic algorithms and return to the CTRU the relevant records via secure file transfer or data interrogation system. The occurrence of clinical events will not be centrally adjudicated, since the EHR do not include access to the detailed hospital notes. We will investigate the effect of discrepancies between the EHR and the data reported on the CRFs, on the trial results in a sensitivity analysis.

Data received via CRFs will be entered onto a dedicated CTRU database (MACRO, InferMed) which will include validations to identify missing or discrepant data. The trial statistician will download accumulated data to identify discrepant data items for investigation. Data received via EHR will be automatically uploaded to the MACRO database via a data import system.

### Statistical methods

#### Sample size

A minimum of 30 clusters, each recruiting 100 participants (ie, 3000 in total) will give 80% power to detect clinically relevant differences in the co-primary endpoints with two-sided 5% significance tests (see sections 7.2.1 and 7.2.3 of^34^). For the proportion of class I guideline-recommended therapies implemented, this assumes 95%^35^ of recommended therapies implemented in the control arm and will detect an absolute increase of 3% to 98% in the GRACE arm, with an assumed coefficient of variation (CV) in cluster outcomes of 0.02. For time to first cardiac outcome, a fixed recruitment of 15 clusters of 100 patients per arm gives 80% power to detect a difference in 12 month rates of 13% and 10.4% between standard care and GRACE arms, assuming a mean follow-up of 27 months and CV of cluster event rates of 0.05. Both endpoints require 14 clusters of 100 patients in each arm to have 80% power, though no adjustment for multiple testing was made. Recruiting 15 clusters per arm allows for attrition of 7% to 10%. For more details, see online supplementary file 3. Additional sites have been and will be opened to ensure that target recruitment is achieved, and to safeguard study power should these assumptions not be met.

10.1136/bmjopen-2019-032165.supp3Supplementary data

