### Trial status

The first site opened to recruitment on 13^th^ February, 2017, and the first patient was recruited on 13^th^ March, 2017. At the time of manuscript submission, 39 hospitals had been randomised to a study arm (of which 30 have registered at least one patient), and 2515 patients had consented to take part. Recruitment is expected to end on 31^st^ December, 2019, with end of follow-up ending on 31^st^ December, 2020, and completion of analysis by 30^th^ June, 2021.

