### Outcome measures

There are two co-primary endpoints: (i) the uptake of class I guideline-indicated therapies (specifically, the 11 listed in online supplementary file 2) and (ii) the composite of cardiovascular death, non-fatal myocardial infarction, hospitalisation for new onset heart failure or cardiovascular readmission, at 12 months (table 1, with subsequently derived outcome measures in table 2). Secondary endpoints are total duration of inpatient stay, quality of life based on EQ-5D-5L^28^ responses and utilities, unscheduled coronary revascularisation and the components of the composite endpoint over 12 months follow-up.

10.1136/bmjopen-2019-032165.supp2Supplementary data

**Table 1 T1:** Schematic of assessments

TIME POINT*	Cluster identification	Cluster allocation	Patient identification	Patient registration	Post-allocation		
	*-t_3_*	*-t_2_*	-t_1_	*0*	*t_A_*	*t_D_*	***12*** m
CLUSTER ENROLMENT:							
Eligibility screen	X						
Essential documents	X						
Randomisation		X					
Site initiation		X					
PATIENT ENROLMENT:							
Eligibility			X				
Informed consent			X				
Registration				X			
INTERVENTIONS:							
GRACE/CRUSADE risk scoring (X) and subsequent care					X		
Standard care					X		
ASSESSMENTS:							
Baseline assessments*				X			
EQ-5D-5L				X			X
Edmonton frailty score				X			
Numbers of class I guideline indicated therapies					X		
Numbers of therapies received						X	X
Date of discharge						X	
Final diagnosis						X	
Medications prescribed acutely during hospital stay or on discharge						X	
In-hospital cardiovascular procedures						X	
In-hospital outcomes						X	
Other cardiac investigations and treatments						X	
Health advice given						X	
Hospitalisations							X
Deaths							X
Unscheduled revascularisations							X

*Time points: -t_3_, -t_2_, -t_1_ are three arbitrary time points that occur at any time (but in the given order) prior to individual patient enrolment at time 0. Post registration, t_A_ and t_D_ are the time points at which a participant is assessed according to the cluster-randomised strategy and discharged from hospital. Subsequent follow-up is at 12 months.

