**Co-primary**		
(1) Number of class I guideline indicated processes received per patient (see online supplementary file 2 for full description)	Discharge	Logistic regression, modelling agreement between eligibility and receipt of process as function of treatment arm, including fixed effects for minimisation factors, random hospital effect and random patient effect.
(2) Time from registration until first occurrence of one of the following * cardiac death, * new onset heart failure, * non-fatal MI, or * cardiovascular hospitalisation	12 months post registration	Kaplan-Meier survival estimates; appropriate time-to-event regression (eg, proportional hazards, flexible parametric model^47^) including fixed effects for minimisation factors and random hospital effect, (sensitivity analysis: also accounts for competing risks of non-cardiac death and withdrawal from follow-up.)

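### The 80% power for the clinical co-primary rests on 27 months' mean follow-up, but the endpoint is fixed at 12 months, where the same design has about 51–56% power

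*Protocol article*

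**What the plan says.** The Sample size section of the protocol article claims "80% power to detect clinically relevant differences in the co-primary endpoints with two-sided 5% significance tests" from 30 clusters of 100 patients. For time to first cardiac outcome it says that "a fixed recruitment of 15 clusters of 100 patients per arm gives 80% power" for a "difference in 12 month rates of 13% and 10.4% between standard care and GRACE arms". The exposure and clustering inputs behind that claim are given as "assuming a mean follow-up of 27 months and CV of cluster event rates of 0.05". The section adds that 14 clusters per arm suffice for either co-primary, "though no adjustment for multiple testing was made", and that the fifteenth cluster covers attrition of 7% to 10%.

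The endpoint is defined over a shorter period. Outcome measures lists the composite as including "hospitalisation for new onset heart failure or cardiovascular readmission, at 12 months". Table 2 gives the assessment time of co-primary (2) as "12 months post registration". The abstract and the Objectives also say 12 months, and the footnote to Table 1 places the only follow-up after discharge at 12 months. Trial status has recruitment ending on 31 December 2019, "with end of follow-up ending on 31^st^ December, 2020", which is 12 months after the last patient enters.

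**The concern.** The power of a comparison of event rates is driven by the number of events, and so by person-time. A mean of 27 months credits each patient with 2.25 person-years. An endpoint that closes at 12 months allows at most 1. Nothing in the article provides for counting events after month 12 in this endpoint. The calculation therefore uses more than twice the exposure that the defined endpoint can supply.

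This is one of two co-primary endpoints and the only one that measures clinical events. If the stated power does not apply to it, readers of the protocol have the wrong figure for the trial's chance of detecting its own target effect, and a non-significant result would be interpreted against that wrong figure.

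**Working it through.** **Inputs (Sample size section).** Rates r0 = 0.13 and r1 = 0.104, difference d = 0.026 (a 20% relative reduction). Between-cluster CV k = 0.05. Two-sided 5% test, 80% power, so (1.96 + 0.8416)² = 7.849. Clusters of 100 patients, 15 per arm.

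**Formulae (standard unmatched cluster-trial formulae).**
- Clusters per arm: c = 1 + 7.849 × V / d².
- Power with c clusters per arm: Φ(√[(c − 1) d² / V] − 1.96).
- For rates: V = (r0 + r1)/y + k²(r0² + r1²), where y is person-years per cluster.
- For proportions with 100 patients per cluster: V = [p0(1 − p0) + p1(1 − p1)]/100 + k²(p0² + p1²).
- The clustering term is the same throughout: 0.0025 × (0.0169 + 0.010816) = 0.0000693.

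**1. The plan's own figure, 27 months.** y = 100 × 27/12 = 225. V = 0.234/225 + 0.0000693 = 0.0011093. c = 1 + 7.849 × 0.0011093/0.000676 = 13.88, so 14 clusters, as stated. Power is 80.4% with 14 clusters and 83.2% with 15.

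**2. Twelve months, rates.** y = 100. V = 0.234/100 + 0.0000693 = 0.0024093. c = 28.97, so 29 clusters per arm. With 15 clusters, √(14 × 0.000676/0.0024093) = 1.982 and power = Φ(0.022) = 50.9%. With 14 clusters it is 48.0%.

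**3. Twelve months, proportions.** V = (0.1131 + 0.093184)/100 + 0.0000693 = 0.0021321. c = 25.76, so 26 clusters per arm. With 15 clusters, √(14 × 0.000676/0.0021321) = 2.107 and power = Φ(0.147) = 55.8%. With 14 clusters it is 52.8%.

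**4. Sensitivity to convention (12 months, 15 clusters per arm).**

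| Convention | Power |
|---|---|
| Noncentral t, 28 df | 50.8% (rates), 55.8% (proportions) |
| Without the extra cluster (the +1) | 53.6% (rates), 58.7% (proportions) |
| 12-month risks converted to hazards (0.139, 0.110) | 58.5%; 61.4% without the +1 |
| Same hazards, person-time cut at first event | 56.0% |
| No clustering, 1500 per arm, two proportions | 60.1% |

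**5. What 80% power would take at 12 months.** Either 26–29 clusters of 100 per arm (26 × 2 × 100 = 5200 to 29 × 2 × 100 = 5800 patients, not 3000) or a larger effect. With 15 clusters per arm and 13% in the control arm, solving the power formula for r1 gives 9.4% (rates) or 9.6% (proportions), a relative reduction of about 28% or 26%.

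**The case against.** The strongest reply is that the calculation may have been made for an analysis running to a common closing date. Co-primary (2) is analysed by time-to-event methods. If accrual were uniform from 13 March 2017 to 31 December 2019 (about 33.6 months) and everyone were followed to 31 December 2020, mean follow-up would be 12 + 33.6/2 = 28.8 months, close to 27. Supplementary file 3, which is not shown, may explain the figure, and the SAP will carry the derivations. This makes the origin of the 27 months plausible, but it does not make the stated power apply to an endpoint that the article fixes at 12 months. The article misdescribes either the analysis horizon or the power.

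A second reply is that additional sites are being opened to protect power. The 80% is claimed for 30 × 100, however. If all 39 randomised hospitals (19.5 per arm) recruited 100 patients each, 12-month power would still be only about 62–68%.

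Three stronger readings do not hold.
- A reader might infer an arithmetic slip. The stated 14 clusters follow correctly from the stated inputs; the fault is an input that conflicts with the endpoint.
- A reader might infer that power falls short even at 27 months, because person-time stops at the first event. That gives about 78% with 15 clusters only if 13% and 10.4% are read as constant hazards. Read as 12-month risks, the same calculation gives 85%.
- A reader might infer that the linked records already cover follow-up beyond 12 months. The article does not say so: the closing date is exactly 12 months after the last recruitment, and Monitoring describes review of outcomes until 12 months.

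**Conclusion.** The point holds as an inconsistency between the sample-size assumption and the endpoint definition. For the endpoint as defined, the stated 80% is wrong: 15 clusters of 100 per arm give about 51% (rates) to 56% (proportions). Reasonable conventions span roughly 50–60%, with a ceiling of about 61%. Since power is only 60% with no clustering at all, the conclusion does not depend on the assumed CV or on the choice of formula.

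It rests on the article's own rates, CV and cluster size, and on complete 12-month follow-up in all 15 clusters per arm. With 14 clusters, as after the attrition allowance, power is 48.0% (rates) or 52.8% (proportions). The article does not show whether the horizon or the power statement is the one in error, so the passages have to be reconciled.

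**What to change.** Reconcile the Sample size section with the Objectives, Outcome measures and Table 2 before any comparative analysis.

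- **If the 12-month endpoint stands:** remove the 27-month assumption from the power statement. Restate power for 13% versus 10.4% as about 51–56% (50–60% depending on convention), and give the difference detectable with 80% power at 12 months, about 13% versus 9.4–9.6%. This costs wording only, and a less favourable stated power.
- **If an analysis over all follow-up to a common closing date was intended:** state this in the endpoint definition and Table 2 by a dated amendment, and keep the 12-month analysis. First confirm that consent and record linkage extend beyond 12 months. No new patients are needed, but the cost is real. It changes the estimand of a co-primary endpoint in an open-label trial with 2515 patients already consented, and alignment with the harmonised Australian and Canadian trials would need checking.

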#### Analysis methods

A full statistical analysis plan will be finalised prior to any comparative analyses, following the guidelines of Gamble *et al*.^36^ The statistical analysis plan will describe the derivation of outcomes, define analysis populations and detail the analyses of each outcome measure. In brief, analyses will take the form of generalised linear models that include fixed effects for the minimisation/stratification factors and random effects for the recruiting hospitals (the random effects distribution with the best statistical fit will be used for analysis) to reflect the cluster-randomised nature of the trial (table 2). The derivation of the primary outcome measure is defined in online supplementary file 2. Additional exploratory subgroup analyses are planned for the primary endpoint: analysing guideline uptake according to intervention type (invasive, non-invasive, behavioural and pharmacotherapies); subgroup effects will investigate interaction between treatment arm and age, gender, diabetes, heart failure, initial hospital type, frailty, comorbidity and estimated bleeding risks, among others. Analyses will use the full analysis set comprising all registered participants analysed according to their randomised hospital as intention to treat (patients will only be excluded if informed consent was not given, or if participants request that their data not be used in any analysis). Further supporting randomisation-respecting efficacy analyses may be considered, in particular, a mediation analysis^37^ to estimate the net direct and net indirect effects of a non-NSTEACS final diagnosis on receiving class I guideline therapies. The statistical analysis plan will include an agreed strategy for imputing missing data items (using multiple imputation, where appropriate^38 39^), including handling incomplete EHR on cardiovascular registries and other data sources to determine whether absent records indicate no events.

### Monitoring

Oversight of the trial will be the responsibility of the independent Trial Steering Committee (TSC), comprising two independent cardiologists, an independent statistician and one independent patient representative. An independent Data Monitoring and Ethics Committee (DMEC) will meet to review accumulating safety and compliance data from the UKGRIS trial. The members will comprise an independent statistician and three independent cardiologists. There are no planned interim analyses of efficacy for the UKGRIS trial. The members of the Trial Management Group, the DMEC and the TSC are listed in online supplementary file 4.

10.1136/bmjopen-2019-032165.supp4Supplementary data

Given that the intervention carries minimal risk to participants, serious and non-serious unrelated or expected adverse events will not be reported. Instead, participant primary and secondary outcomes at the time of discharge from hospital (or death if it occurs during hospitalisation) until 12 months will be reviewed by the DMEC at a site level using CRFs and EHRs. All related and unexpected serious adverse events occurring from the date of consent up to 3 months following admission will be sent to the CTRU within 24 hours of the clinical research staff becoming aware of the event. Changes to the protocol will be provided to the Research Ethics Committee for review. On receipt of favourable opinion, new versions of the protocol will be communicated to sites for implementation. Sites randomised to routinely employ the GRACE risk score tool will be able to note where particular guideline-recommended therapies are deemed not appropriate. All sites will be able to report that guideline-recommended invasive strategies are not appropriate.

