### Interventions

#### GRACE risk score tool

Consenting participants recruited from hospitals in the intervention arm will receive care determined by staff trained to use the GRACE risk score tool and provided with a paper scoring table. Each consenting participant will have their risk score and corresponding 6 month mortality risk estimated by the appointed healthcare professional within 12 hours of hospitalisation. GRACE risk scores are categorised as ‘low’ (0 to 108), ‘intermediate’ (109 to 140) or ‘high’ (≥141), and the risk score nomogram (figure 2) will list recommended therapies (including pharmacological, invasive, non-invasive and behavioural interventions and tests) for patients based on their risk category (figure 3). At the same time as the GRACE risk score is calculated, sites will complete the CRUSADE bleeding risk score (Can Rapid risk stratification of Unstable angina patients Suppress ADverse outcomes with Early implementation of the ACC/AHA Guidelines).^27^ Both GRACE and CRUSADE will be completed using pen and paper scoring tables provided by the CTRU, online scoring applications and websites will not be used. Figure 2 illustrates the GRACE risk score nomogram as used in UKGRIS, while figure 3 illustrates the resulting recommendations arising from the scores obtained. Sites are invited to justify their decisions in declining to follow a recommendation on the grounds of contraindication. As part of the site initiation process, intervention sites will be informed as to how to complete the GRACE risk score paper nomogram, and follow its resulting recommendations. Sites will be monitored by telephone interviews with the ‘site champion’ throughout recruitment to ensure that GRACE and CRUSADE scoring is still routinely used for managing patients with NSTEACS. If GRACE sites stop routinely using the GRACE and CRUSADE risk scores, they will be asked to resume their use, and to cease recruitment to the UKGRIS trial if they fail to do so.

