#### Standard care

Hospitals randomised to standard care will treat patients according to local practice (without using the GRACE risk score tool and associated clinical prompts) (figure 1). Sites will be monitored by telephone interviews with the ‘site champion’ throughout recruitment to ensure that processes for managing patients with NSTEACS are unchanged and that the management according to the GRACE risk score has not been systematically implemented due to a change in hospital policy. Standard care-assigned sites should not be routinely using the GRACE risk score nor the CRUSADE bleeding risk score to manage NSTEACS patients while taking part in the trial. Standard care sites implementing either scoring system during the study (as identified during regular site monitoring updates) will be asked to cease use and will stop recruitment to the UKGRIS trial if routine use continues.

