**Secondary**		
(1) Health-related quality of life (EQ-5D-5L utility)	12 months post registration	Linear regression, (with data transformed, if necessary) including fixed effects for minimisation factors and baseline value with random hospital effect.
(2) Number of days in hospital within 12 months	12 months post registration	Linear regression (with data transformed, if necessary) including fixed effects for minimisation factors and random hospital effect.
(3) Time until first occurrence of each component of the composite co-primary endpoint (co-primary (2)). Performed separately for each of the four components.	12 months post registration	Kaplan-Meier survival estimates; time-to-event regression including fixed effects for minimisation factors and random hospital effect, accounting for (sensitivity analysis: competing risks of non-cardiac death and withdrawal from follow-up.)
(4) Unscheduled revascularisations. Any admission (1=Yes, 0=No) for an unplanned PCI or CABG within 12 months of registration.	12 months post registration	Logistic regression, including fixed effects for minimisation factors with random hospital effect.

CABG, coronary artery bypass graft; MI, myocardial infarction; PCI, percutaneous coronary intervention; UKGRIS, UK GRACE Risk Score Intervention Study.

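### No bleeding outcome is pre-specified and expected or unrelated adverse events go unreported, so no between-arm comparison of bleeding is planned

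*Protocol article*

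**What the plan says.** **Intervention.** Under *GRACE risk score tool*, the chart lists recommended therapies by risk category, pharmacological and invasive ones among them. Bleeding risk is scored too: "At the same time as the GRACE risk score is calculated, sites will complete the CRUSADE bleeding risk score". Under *Standard care*, control sites should routinely use neither the GRACE score "nor the CRUSADE bleeding risk score to manage NSTEACS patients while taking part in the trial".

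**Outcomes.** Under *Outcome measures*, one co-primary is uptake of class I therapies and the other is "the composite of cardiovascular death, non-fatal myocardial infarction, hospitalisation for new onset heart failure or cardiovascular readmission, at 12 months". The secondary endpoints are total inpatient stay, EQ-5D-5L, "unscheduled coronary revascularisation and the components of the composite endpoint over 12 months follow-up". Table 2 repeats this list. The *Discussion* names mortality as the key safety outcome.

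**Bleeding in the analysis.** Bleeding appears only as a baseline risk. The exploratory subgroup factors in *Analysis methods* end with "frailty, comorbidity and estimated bleeding risks, among others".

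**Safety reporting.** *Monitoring* states: "Given that the intervention carries minimal risk to participants, serious and non-serious unrelated or expected adverse events will not be reported". In place of such reporting, the Data Monitoring and Ethics Committee (DMEC) reviews the primary and secondary outcomes to 12 months, by site, from case record forms (CRFs) and electronic records. What remains reportable is narrow: "All related and unexpected serious adverse events occurring from the date of consent up to 3 months following admission will be sent to the CTRU". The same section also gives the DMEC a general remit over accumulating safety and compliance data.

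**The concern.** A trial of a prompt to treat should be able to show what the extra treatment costs as well as what it gains. Here the arms differ in two ways that bear on bleeding: the prompts for drug and invasive therapy, and the formal scoring of bleeding risk. The first could raise bleeding and the second could lower it. The protocol treats bleeding as relevant enough to score at every intervention site, but plans no comparison that would show which way it moved.

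The only reason given for the light safety reporting is that the intervention carries minimal risk. The sample size, however, rests on the tool cutting the 12-month event rate from 13% to 10.4%, a relative fall of 2.6/13 = 20%. A tool assumed to change care enough to do that cannot be taken in advance to leave the harms of that care unchanged.

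At stake is the conclusion on net benefit. A favourable result on both co-primaries would be reported with no matching estimate for the main plausible counter-effect.

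**Working it through.** **1. Where a bleed could enter the plan**

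| Place | What happens to a bleed |
|---|---|
| Co-primary 1 (processes received, at discharge) | Not counted |
| Co-primary 2 (Table 2) | No bleeding component; the article gives no coding definition of cardiovascular readmission |
| Secondary: "Number of days in hospital within 12 months" | The stay adds days, mixed with stays for any other cause |
| Secondary: EQ-5D-5L at 12 months | May lower a survivor's score; cause not identified |
| Secondary: revascularisation and the composite's components | No bleeding item |
| Sensitivity analysis for co-primary 2 | A fatal bleed classed as non-cardiac is a competing event |
| Bleeding-risk subgroup | Baseline effect modifier, not an outcome |
| Adverse event reporting | Only if serious, related and unexpected, and within 3 months of admission |
| CRF in-hospital outcomes (Table 1) | Contents not shown; collected at discharge |

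No row yields a bleeding count by arm to 12 months. Inpatient days cannot stand in for one, because fewer cardiovascular stays could hide more bleeding stays. Adverse event reporting cannot either. It covers roughly 3 of the 12 months, and site staff who know their allocation would have to judge relatedness to a tool that control sites do not use.

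**2. The plan's own sample size, to confirm the method**

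Inputs from *Sample size*: 100 patients per cluster, two-sided 5%, 80% power, so f = (1.96 + 0.84)² ≈ 7.85. Here c is clusters per arm and k the coefficient of variation between clusters.

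- Proportions: c = 1 + f[p0(1-p0)/m + p1(1-p1)/m + k²(p0² + p1²)]/(p0-p1)². With p0 = 0.95, p1 = 0.98, m = 100, k = 0.02: c = 1 + 7.85 × 0.001416/0.0009 = 13.35, so 14.
- Rates: c = 1 + f[(r0 + r1)/y + k²(r0² + r1²)]/(r0-r1)². With r0 = 0.13, r1 = 0.104, k = 0.05 and y = 100 × 27/12 = 225 person-years: c = 1 + 7.85 × 0.001109/0.000676 = 13.88, so 14.

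Both match the stated 14 clusters per arm. Neither figure concerns bleeding; they show only that the formulas are the plan's.

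**3. What a bleeding outcome could show**

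The documents give no bleeding risk, so control risks of 3% and 5% and k from 0 to 0.25 are assumptions. Solving the proportions formula for p1 with c = 15 and m = 100:

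| Assumed control risk | Control events per 1500 | Smallest p1 with 80% power | Relative rise | Extra events per 1500 |
|---|---|---|---|---|
| 3% | 45 | 5.1-5.4% | 69-81% | 31-36 |
| 5% | 75 | 7.6-8.2% | 51-64% | 39-48 |

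Check at 3%, k = 0, p1 = 0.0508: 14 × 0.0208²/(0.000291 + 0.000482) = 7.8, as required.

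For scale, the targeted benefit, read as 12-month proportions, is 0.026 × 1500 = 39 patients. The bleeding excess detectable with 80% power is therefore about as large, in patients, as the benefit sought.

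**The case against.** The case on the other side has real force on several points.

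- **A reader might infer that bleeding is counted nowhere.** The documents do not support this. A bleeding readmission adds to inpatient days, and hospitalisations and causes of death are collected in both arms. What is missing is a named comparison, not the data.
- **A reader might infer that bleeding never reaches the DMEC.** The article does not say so. The DMEC also has the general safety remit, and the CRF's in-hospital outcomes may include bleeding.
- **A reader might infer that bleeds will be dropped as expected.** The article shows no list of expected events, and it condenses a full protocol that is not shown. A serious, related, unexpected bleed within 3 months is reportable.
- **The bleeding-risk subgroup is legitimate.** Using baseline bleeding risk as an effect modifier is not an error.
- **The effect may be small, or go the other way.** The planned rise in therapy delivery is 95% to 98%, or 3/95 = 3.2% in relative terms. If bleeding rose in proportion from 3-5%, that would be 45 × 0.032 = 1.4 to 75 × 0.032 = 2.4 extra bleeds per 1500. Proportionality is only an illustration, since the plan itself assumes a 20% relative effect on events. Still, sites may decline a therapy as contraindicated, and the bleeding score may itself reduce bleeding.
- **Such detail belongs in the analysis plan.** This is only partly right. Derivation and modelling do belong there, but the article presents its endpoint list as complete and describes the analysis plan as deriving and analysing outcomes, not adding them.

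These points narrow the concern. They do not supply a between-arm bleeding comparison.

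**Conclusion.** The concern holds in a limited form. The endpoint list contains no bleeding outcome, mortality is the only named safety outcome, and the review that replaces adverse event reporting covers that same endpoint list. Followed as written, the plan gives no comparison of bleeding between arms.

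Two stronger conclusions should not be drawn. The first is that the trial cannot show net benefit or harm: inpatient days, EQ-5D-5L and the competing-risk analysis absorb part of any bleeding effect, though none identifies it. The second is any figure for how much of the benefit bleeding would cancel, because the documents give neither a bleeding rate nor an expected change, and the direction is unknown.

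The sizes above rest on the assumed 3-5% control risk and k of 0 to 0.25. They describe precision, not expected harm. The gap should be closed because it limits what can be concluded about net benefit. It does not invalidate either co-primary analysis.

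**What to change.** Add one safety row to Table 2: time to first hospitalised or fatal bleeding within 12 months of registration.

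- **Derivation:** one code list fixed before any comparative analysis and applied identically in both arms to the hospital episode and death records already requested under *Data collection*. Add the discharge CRF if it records in-hospital bleeding.
- **Analysis:** the time-to-event model already used for co-primary 2, with the minimisation factors and hospital random effect. Report it by arm as an estimate with a confidence interval beside the clinical co-primary.
- **Oversight:** add it to the outcomes the DMEC reviews.

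The cost is a table row, a code list and an analysis of records already linked, with no new patient contact. If the CRF does not record bleeding in the index stay, one added item may be needed.

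The limits should be stated in the plan. Coded bleeding is unadjudicated and misses minor bleeds. The trial can estimate a moderate increase but not exclude one, so a non-significant result must not be read as absence of harm. Defining the outcome now would also let it be carried into the planned international individual-patient meta-analysis, where precision may be better.
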